| Intervention and comparator | 252-255 & 440-443      | In the intervention group, four interventions will be implemented at one-month intervals, each followed by an evaluation of quality of life and mental health status outcomes. The four evaluations in the intervention group will run concurrently with those in the control group. The intervention will be implemented by trained Health promoters utilising the Motivational Interviewing Training New Trainers Manual, along with a pocket guide for motivational interviewing and a participant's manual on substance abuse, during the intervention.                                                                                                                                                                           | 10,19  |
|                             | N/A                    | Criteria for discontinuing or modifying allocated intervention/comparator for a trial participant (e.g., drug dose change in response to harms, participant request, or improving/worsening disease)                                                                                                                                                                                                                                                                                                                                                                                                                                                                                                                                  | N/A    |
|                             | 447-551                | To enhance adherence to the mental wellness intervention, participants will receive regular SMS and phone call reminders before each health promoter-led session to support adherence. Attendance will be tracked, with follow-ups conducted within a week for those who miss sessions. Health promoters will offer motivational counselling and brief check-ins, while session logs will record engagement and barriers to ensure the intervention is delivered as intended.                                                                                                                                                                                                                                                         | 19     |

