|                             | 255-269

364-367 | 
The control group will continue to receive the usual care for cervical cancer treatment. At the end of the intervention period, the participants with cervical cancer in the control group will be revisited for outcome measures. They will further be referred to health facilities for definitive diagnosis and management of their mental health if at risk.
 
Referral pathways to psychiatric or crisis services are in place for those mental health patients who are excluded, ensuring they are not left without support. Notwithstanding, patients living with cervical cancer who have suicidal ideation may benefit from integrated mental health services, and their exclusion could delay access to care
    | 10, 15 |
| Outcomes                    | 242-245                | Primary outcomes: quality of life, and mental health indicators (anxiety and depression scores - GAD-7 and PHQ-9) will be evaluated in both groups as primary outcomes.                                                                                                                                                                                                                                                                                                                                                                                                                                                                                                                                                               | 9      |
|                             | 244-245                | Secondary outcomes will include attendance rate, retention, and data completeness at intervention sessions.                                                                                                                                                                                                                                                                                                                                                                                                                                                                                                                                                                                                                           |        |

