| Harms                       | 516-521                | The study will abide by the four ethical principles of Autonomy, Non-maleficence, Beneficence, and Justice. In this study, potential harms are described as emotional distress or psychological fatigue experienced by participants during mental wellness sessions. No physical harm is expected. Harms                                                                                                                                                                                                                                                                                                                                                                                                                              | 21     |

|                                             |         |                                                                                                                                                                                                                                                                                                                                                                                                                                                                                                                                                                                                                                                    |       |
|---------------------------------------------|---------|----------------------------------------------------------------------------------------------------------------------------------------------------------------------------------------------------------------------------------------------------------------------------------------------------------------------------------------------------------------------------------------------------------------------------------------------------------------------------------------------------------------------------------------------------------------------------------------------------------------------------------------------------|-------|

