|                                             |         | will be monitored through emotional check-ins, supervision meetings, and participant reports. All concerns will be documented, reviewed, and addressed following ethical guidelines for participant safety.                                                                                                                                                                                                                                                                                                                                                                                                                                        |       |
| Participant timeline                        | 252-255 | In the intervention group, four interventions will be implemented at one-month intervals, each followed by an evaluation of quality of life and mental health status outcomes. The four evaluations in the intervention group will run concurrently with those in the control group.                                                                                                                                                                                                                                                                                                                                                               | 10    |
| Sample size                                 | 286-299 | $n = \frac{(\sigma_1^2 + \sigma_2^2)(Z_{1-\alpha} + Z_{1-\beta})^2}{(\mu_1 - \mu_2)^2}$ 
The sample size was calculated using the equation, for a two-sided 95% confidence interval, where <math>\alpha = 0.05</math>, <math>Z_{1-\alpha} = 1.96</math>, and for 80% power, <math>Z_{1-\beta} = 0.84</math>. The mean difference <math>\mu_1 - \mu_2 = 1</math> and the standard deviation (<math>\sigma</math>) = 2. The sample size was calculated using a two-sample means formula, assuming a mean difference of 1 and a standard deviation of 2, which corresponds to a medium standardized effect size (Cohen's <math>d = 0.5</math>).
 | 12-13 |

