| Sequence generation                         | 284-287 | $n = \frac{(\sigma_1^2 + \sigma_2^2)(Z_{1-\alpha} + Z_{1-\beta})^2}{(\mu_1 - \mu_2)^2}$ 
The sample size was calculated by the Biostatistician using the equation for a two-sided 95% confidence interval, where <math>\alpha = 0.05</math>, <math>Z_{1-\beta} = 1.96</math>, and for 80% power, <math>Z_{1-\beta} = 0.84</math>. The mean difference <math>\mu_1 - \mu_2 = 1</math> and the standard deviation (<math>\sigma</math>) = 2
                                                                                                                                                                                                    | 12    |
|                                             | 317-359 | Cluster randomising at the hospital level (rather than individual level) will be employed to select patients with a cervical cancer diagnosis at both Nelson Mandela Academic and Saint Elizabeth hospitals to participate in a survey on their quality of life and their mental health status, specifically screening for depression and anxiety.                                                                                                                                                                                                                                                                                                 | 13-14 |
| Allocation concealment mechanism            | 337-359 | To ensure allocation concealment and minimise selection bias, the randomisation process will be managed independently by a designated biostatistician and data capturer who will not be involved in participant recruitment or data collection. The random allocation sequence will be securely stored in a password-protected electronic system. The interventions and data collection will be conducted independently at each hospital. Participants will be randomly assigned to two groups, with 64 participants in each of the intervention and control groups.                                                                               | 14    |

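### Harm is described only as distress or fatigue during sessions that the intervention arm alone attends, so harm records alone cannot separate session effects from background distress

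*Protocol*

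**What the plan says.** The Harms row says that "potential harms are described as emotional distress or psychological fatigue experienced by participants during mental wellness sessions", adds that physical harm is not expected, and continues that harms "will be monitored through emotional check-ins, supervision meetings, and participant reports". It closes with a general undertaking: "All concerns will be documented, reviewed, and addressed following ethical guidelines for participant safety". No other description of harm appears in the document at hand.

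The Intervention and comparator row gives the intervention group four health promoter-led sessions, one month apart, each followed by an evaluation. For the other arm it says: "The control group will continue to receive the usual care for cervical cancer treatment". On contact with controls it says both "The four evaluations in the intervention group will run concurrently with those in the control group" and "At the end of the intervention period, the participants with cervical cancer in the control group will be revisited for outcome measures".

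The Outcomes row states that quality of life, GAD-7 and PHQ-9 "will be evaluated in both groups as primary outcomes". The Allocation concealment row sets the arm sizes, "with 64 participants in each of the intervention and control groups". The Data monitoring committee row provides for continuing attention to participants' well-being, mentions interim safety summaries, and lists harm and participant welfare among the grounds for early termination.

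**The concern.** What counts as harm is tied to an activity that one arm does not have. Distress is to be expected in women treated for cervical cancer whether or not they attend sessions; the protocol itself plans mental-health referral for controls found to be at risk. When harm is recognised only inside sessions, background distress voiced there looks like an effect of the sessions. Distress that follows a session by some days falls outside the description. Whoever reads the safety summaries would have intervention-arm records with no control-arm counterpart to set them against. What is at stake is the interpretation of harm records. The primary efficacy comparison is not affected.

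**Working it through.** **Arm size.** The protocol's formula with its own inputs gives (2² + 2²) x (1.96 + 0.84)² / 1² = 8 x 7.84 = 62.72, so 63 per arm. The protocol uses 64. Nothing here depends on the difference, and 64 is used below.

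**Opportunities for a record that fits the description.** Sessions per participant times participants (Intervention and comparator row; Allocation concealment row):
- Intervention: 4 x 64 = 256 planned session contacts.
- Control: 0 x 64 = 0.

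These count opportunities. They are not expected events.

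**Does any other text widen the description or set a common procedure?**
- *Channels in the Harms row.* No arm is named. The only check-ins described elsewhere are those that health promoters offer as adherence support for the intervention (Intervention and comparator row). Participant reports could come from either arm, but nothing says when or how controls are asked.
- *The undertaking to document all concerns.* It is not limited to an arm or to sessions, so it may capture distress in controls. It does not call such distress harm, and it sets no question or schedule.
- *Well-being monitoring and early termination (Data monitoring committee row).* These apply to the whole trial, but give no second description of harm and no collection procedure.
- *Separate supervision structures for each arm (Blinding row).* This stands beside limits on sharing materials between clusters. It gives controls no sessions and no harm enquiry.
- *PHQ-9 and GAD-7 (Outcomes row).* Both arms are scored, as primary outcomes. No degree of worsening is designated as harm.

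None of the five changes the result.

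**Occasions already available for a common item.** There are 128 participants, 64 per arm.
- If the four concurrent evaluations hold: 4 x 128 = 512 evaluations, 256 per arm.
- If controls are seen only at the end of the intervention period: 1 x 128 = 128 common evaluations, 64 per arm.

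On either reading there is at least one evaluation at which both arms can be asked the same thing.

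**The case against.** The Harms row can be read as naming the risk expected from the intervention rather than as a rule on what may be logged. The same row promises to document all concerns, and well-being is watched throughout. PHQ-9 and GAD-7 are scored in both groups, so a general worsening of mood caused by the sessions should appear in the primary comparison. The protocol plans no between-arm test of harms, and tabulation by arm could be left to a statistical analysis plan. The document at hand is also a checklist that points to a manuscript not shown.

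Much of this stands. Distress in controls may be noticed and handled, and no planned analysis is biased by the wording. Two things remain. An analysis plan can tabulate only what was collected, and what counts as harm and how it is elicited are fixed here, in session-bound terms. And data from both arms on mood scales do not serve as a harms record until some degree of worsening is designated as harm.

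A reader might infer more: that distress outside sessions goes unseen, or that early stopping hangs on this one sentence. The documents do not support either. The general safeguards cover the first, and participant welfare is a separate ground for termination.

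**Conclusion.** The point holds in a limited form. As described, harm can be recorded only in the intervention arm and only during sessions: 256 planned contacts against none. No stated procedure collects distress alike in both arms, so harm records alone cannot separate the effect of the sessions from background distress.

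This rests on two readings: that the mental wellness sessions are the four health promoter-led sessions of the intervention, and that usual care includes none of them. Both follow from the Intervention and comparator row.

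A reader might go further and put a figure on the bias. For example, if 5% to 20% of participants were distressed for unrelated reasons and voiced it in sessions, 64 x 0.05 = 3.2 to 64 x 0.20 = 12.8 would be logged against 0. That only restates assumed rates and assumes that nothing is documented in controls. The protocol gives no rates and plans no such comparison, so no numerical bias can be derived from it. The change is recommended because it is cheap and makes the safety summaries interpretable.

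**What to change.** 1. Define harm without reference to sessions: any emotional distress, psychological fatigue, or worsening of PHQ-9 or GAD-7 beyond a stated threshold, from randomisation to the last evaluation. The protocol gives no threshold; fix one before data collection starts.
2. Derive score worsening from the questionnaires already planned.
3. Ask one identical item about distress and fatigue, worded without mention of sessions and placed after the outcome scales, at each evaluation held in both arms. Restricting it to shared evaluations keeps the opportunity to report equal, and settling whether controls have four evaluations or one fixes how often it is asked.
4. Show the results by arm in the safety summaries. The Sequence generation row also speaks of randomising by hospital; if that is what is done, arm and hospital coincide across the two sites and the table is descriptive only.

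The cost is a reworded definition and one form item, with no added visits. The downside is a small risk that an answer reveals allocation to the blinded outcome assessor. Asking the item last limits the effect on the outcome scales at that visit.

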| Data collection methods                                   | 419, 427-428, 441-443 | A combined total of 128 patients will have their quality of life assessed using the WHO-QoL-BREF instrument (Appendix 7). In addition, participants' depression and anxiety will be screened using the PHQ-9 (Appendix 8) and the GAD-7 (Appendix 9) questionnaires, respectively. Health Promoters will utilise the Motivational Interviewing Training New Trainers Manual, along with a pocket guide for motivational interviewing and a participant's manual on substance abuse, during the intervention.                                                                                                                                                                                                                                                                                                                                                                                                                                                                                                                                                                                                                                                                                                              | 18,19 |

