|----------------------------|---------------------------|--------------------------------------------------------------------------------------------------------------------------------------------------------------------------------------------------------------------------------------------------------------------------------------------------------------------------------------------------------------------------------------------------------------------------------------------------------------------------------------------------------------------------------------------------------------------------------------------------------------------------------------------------------------------------------------------------------------------------------------------------------------------------------------------------------------------------------------------------------------------------------------------------------------------------------------------------------------------------------------------------------------------------------------------------------------------------|--------------|
|                            |                           | be the relative measure of association used. The 95% confidence interval (95% CI) will be used to assess the precision of estimates at the 5% level of significance ( $p \leq 0.05$ ).                                                                                                                                                                                                                                                                                                                                                                                                                                                                                                                                                                                                                                                                                                                                                                                                                                                                                   |              |

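### The 80% power at 64 per arm is computed correctly, but it holds only for individually randomised patients, a 0.5 SD effect and almost no loss, and the protocol secures neither the first nor the last

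*Protocol*

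**What the plan says.** The Sample size row uses the standard formula for comparing two means, "for a two-sided 95% confidence interval" "and for 80% power", "assuming a mean difference of 1 and a standard deviation of 2, which corresponds to a medium standardized effect size". It does not say which score the difference of 1 and the SD of 2 belong to. The Outcomes row has three primary measures: quality of life, PHQ-9 and GAD-7.

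The Randomization row sets recruitment at 128 from two hospitals. The Allocation concealment row assigns participants at random to two groups, "with 64 participants in each of the intervention and control groups". The Sequence generation row says something different: "Cluster randomising at the hospital level (rather than individual level) will be employed". The Blinding rows also speak of clusters.

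The Participant timeline row plans four monthly sessions, each followed by an evaluation. On completeness the Outcomes row says: "Secondary outcomes will include attendance rate, retention, and data completeness at intervention sessions". The Data collection row says: "A combined total of 128 patients will have their quality of life assessed using the WHO-QoL-BREF instrument". For the comparison between groups, the Statistical methods row plans a t-test or rank test on patients, "at the 5% level of significance".

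**The concern.** The sample size formula assumes independent patients who are all analysed. The number it requires is the number to be enrolled, so any material loss over four months takes power below the stated 80%. The protocol treats incomplete follow-up as likely enough to measure it as an outcome.

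The formula also has no term for clustering, while one row says hospitals are the unit of randomisation. If that row describes the trial, the formula belongs to a different design.

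The 80% is the figure on which a reader judges whether the trial can answer its question. If its conditions are not stated, a non-significant result may be given more weight as evidence against an effect than the trial can bear.

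**Working it through.** **Inputs from the protocol.** Two-sided alpha 0.05 (z = 1.96), power 80% (z = 0.84), difference 1, SD 2 (d = 0.5), 64 per arm, two hospitals, patient-level t-test. The protocol rows give no loss rate, intracluster correlation (ICC) or pre-post correlation. Those used below are assumptions.

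**1. The plan's own figure.**
- Formula: n per arm = (2² + 2²)(1.96 + 0.84)² / 1² = 8 × 7.84 = 62.72, so 63.
- Power by the normal approximation: 80.1% at 63 per arm and 80.7% at 64.
- Power by the noncentral t distribution: 79.5% at 63 and 80.1% at 64.

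So 64 is the t-test sample size with no inflation. By the protocol's own formula there is one spare patient per arm (64 − 63), or 1.6%.

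**2. Loss, with individual randomisation and d = 0.5.** The number analysed per arm is 64 × (1 − loss).

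| Assumed loss | Analysed per arm | Power, t-test | Power, normal approximation |
|---|---|---|---|
| 0% | 64 | 80.1% | 80.7% |
| 10% | 57.6 | 76% | 76.5% |
| 20% | 51.2 | 71% | 71.6% |
| 30% | 44.8 | 65% | 65.8% |

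**3. The hospital-level statement.** With two hospitals, hospital randomisation means one hospital per arm. Any difference between the hospitals is then inseparable from the treatment effect, and the between-hospital variance cannot be estimated from the data.

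As an illustration only, take an assumed ICC of 0.01 with 64 patients per hospital:
- Design effect = 1 + 63 × 0.01 = 1.63.
- Effective n per arm = 64 / 1.63 = 39.3.
- Power = Φ(√(39.3/8) − 1.96) = Φ(0.255), about 60%. This is a best case, because it treats the ICC as known.
- Type I error of the planned patient-level test = 2 × [1 − Φ(1.96/√1.63)], about 12% instead of 5%.

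The effective n per arm cannot exceed 1/ICC. Once the ICC passes about 1/62.72 = 0.016, no number of patients in two hospitals reaches 80%.

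**4. Baseline adjustment.** With an assumed correlation of 0.5 between baseline and follow-up, an analysis of covariance (ANCOVA) multiplies the residual variance by 1 − 0.5² = 0.75. The effective d becomes 0.5/√0.75 = 0.577. With 51 analysed per arm (20% loss), power is about 82%.

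**The case against.** **The arithmetic is correct.** This stands. The stated figure reproduces, and the point concerns the conditions under which it holds.

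**The document is a checklist of extracts.** The Sample size row points to more manuscript text than it reproduces, and an allowance for loss or a source for the SD could be in the part not shown. This limits what can be said about the wording. It does not change the count: 128 enrolled is 64 per arm, which is the t-test requirement before any allowance.

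**The protocol also describes individual assignment.** This stands, and it limits the clustering part. A reader might infer that the trial's real power is 60% or less because hospitals are randomised. The document does not support that as a settled fact. It contradicts itself on the unit, the ICC is assumed, and with one hospital per arm the power figure describes an analysis that cannot be carried out.

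**Two further readings go too far.**
- A reader might infer that losing any patient at all breaks the 80%. By the protocol's own formula, one loss per arm still leaves 80.1%, although the t-test gives 79.5%.
- A reader might infer that power collapses because the real scores have SDs well above 2. The protocol gives no such SDs, and it already states d = 0.5, which yields the same n on any scale. What remains is narrower: the raw pair is tied to no instrument.

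**Confidence intervals are planned.** They would show the imprecision of a null result, so the risk of misreading is reduced but not removed.

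**Conclusion.** The concern holds with conditions. The stated 80% is right for 64 individually randomised patients per arm, d = 0.5 on the score tested, and essentially everyone analysed.

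- **Loss.** The figure has no working margin. Under assumed loss of 10% to 30%, t-test power is about 76% to 65%. This holds if randomisation is individual.
- **Unit of randomisation.** The hospital-level statement contradicts individual assignment and does not fit the formula. If hospitals really are allocated, the 80% claim has no basis with two hospitals. The example of about 60% power and 12% type I error rests on an assumed ICC of 0.01 and shows direction only.
- **Effect size.** The difference of 1 and SD of 2 can be interpreted only as 0.5 SD, because no instrument is named. This is a matter of clarity and does not by itself lower power.

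The sample size statement should be corrected, but 128 need not change.

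**What to change.** 1. **Settle the unit of randomisation.** If patients are allocated, say so, stratify by hospital, and bring the Sequence generation and Blinding rows into line. Deleting the cluster wording is sound only if allocation really is individual. If hospitals are allocated, withdraw the 80% claim; rewording cannot remove the confounding of treatment with hospital.
2. **Restate the power**, for example: *64 per arm, individually randomised, gives 80% power for a 0.5 SD difference on one primary score if all are analysed, and about 76% or 71% with 10% or 20% loss.*
3. **Express the effect as 0.5 SD** and name the score it applies to, in place of the unattributed raw difference and SD.
4. **Optional:** make a baseline-adjusted comparison (ANCOVA) the planned between-group analysis. Baseline scores are already collected. Only then quote the higher power, about 82% with 20% loss, and state the assumed correlation of 0.5 beside it.

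**Cost:** if allocation is individual, a rewritten sample size paragraph, matching edits to the randomisation text, and a less favourable stated power, with no extra patients. If hospitals are truly allocated, the cost is larger, because the trial loses its stated power basis.
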